**Analysis method**

The primary outcome is assumed to be a continuous longitudinal variable for which linear regression is appropriate. The model will have two levels: time-points within patients**.** Random effects will be applied to the patient-specific intercepts.

1. Outcome: HADS total score at baseline and 4 months.
2. Fixed effects: trial arm, time-point, arm x time-point, design variables (hospital site, sex), other pre-specified covariates and additional covariates (see Choice of Covariates, below).
3. Random effects: patient.

Time-point will be treated as a discrete variable.

In terms of the covariance matrix chosen for the mixed effects model, both an unstructured and a first order autoregressive covariance matrix will be explored. The one with the lowest Bayesian information criteria will be selected.

Alternative tests if violation of distributional assumptions

See distributional tests below.

Sensitivity analysis

See relevant section below

1. **Analyses of Secondary Outcomes**

Research hypotheses:

There are no significant differences in the secondary outcomes between usual cardiac rehabilitation (CR) and home-based (self-help) metacognitive therapy (MCT) plus usual cardiac rehabilitation at 4 months. For the secondary outcomes, tests of an intervention effect will be assessed using the mixed-effects model interaction between treatment arm and time-point.

| **Secondary outcome** | **Description** |
| --- | --- |
| HADS anxiety score | Score based on summing across the 7 anxiety-specific items from the HADS |
| HADS Depression score | Score based on summing across the 7 depression-specific items from the HADS |
| Metacognitions Questionnaire 30 (MCQ-30), the 5 sub-scale scores | MCQ30 is a 30 item measure of beliefs, responses rated on a 4-point Likert scale. Each of the 5 subscales will be analysed separately – the MCQ30 total score will not be analysed.  **Amendment 24/03/2021**  The above text has been found to have been incorrectly retained from an early draft of the SAP and does not express the final planned analysis of the MCQ-30. The below amendment is made prior to any data unblinding.  The trial will analyse the MCQ-30 total score and the ‘negative beliefs about thoughts concerning uncontrollability and danger’ subscale, in line with the analysis of the Pathway WS2 RCT. In previous work we found the MCQ-30 to have a bifactor structure, consisting of a dominant general factor alongside the five sub-scales. The total score has been selected as an outcome to represent the general factor, and the uncontrollability and danger subscale has been selected  as reflecting the primary mechanism targeted in MCT. The remaining sub-scales are omitted to reduce multiple testing. |
| Cognitive Attentional Syndrome-1r (CAS-1r), total score | A 16 item measure assessing individuals’ metacognitive strategies and knowledge. Scored on a scale from 0 to 100, with higher scores indicating more use of metacognitive strategies or greater conviction in metacognitive beliefs. |
| Impact of Event Scale-Revised | A 22-item measure of trauma-related symptoms associated with specific life events. Participants rate how distressing each ‘difficulty’ has been over the past week with respect to their ‘heart event which occurred recently’. Each item is on a five-point scale ranging from 0 (‘not at all’) to 4 (‘extremely’). The IES-R yields a total score ranging from 0 to 88. |
| EQ-5D-5L | A standardised measure of health-related quality of life across five dimensions: mobility, self-care, usual activities, pain/discomfort and anxiety/depression. Each dimension has five response categories ranging in severity from “no problems” to “extreme problems”.  We will analyse the utility scores derived from the instrument. |
| EQ-5D VAS | Score on the general health Visual Analogue Scale of the EQ-5D |

In addition to the above, further patient data will be collected using the Economic Patient Questionnaire (EPQ), designed to collect data on outpatient services and non-hospital-based health and social care use. The EPQ assesses three areas, namely use of primary and community-based health services, social support services accessed outside the hospital, and aids and equipment used as part of care. The EPQ will be used in the health economics analysis and as such will be covered by the HE Analysis Plan and is not discussed further in the current document.

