**Sample size**

The WS3 pilot trial had a planned total sample size of 108, using 1:1 random assignment to Home-MCT plus usual CR or usual CR alone. Participant allocation was undertaken by a blinded statistician using a sequence based on randomised blocks of size 6 and 4, stratified by site, gender and whether they suffered from anxiety, depression or both.

WS3+ utilised an identical randomisation procedure and was powered to detect an effect size of 0.4 on total HADS score at 90% power, assuming a 0.5 correlation between HADS at baseline and FU 20% drop-out at 4 months follow-up (based on WS2). This indicated a total recruitment target (i.e. including the internal pilot participants) of 123 per arm, aiming to collect 4month FU on 98 of these in each arm.

In March 2020 the UK was put into lockdown as a result of the covid-19 pandemic. Covid interfered with participation in CR and also with the entry of CR attendance data into the database. Since it was unknown how long the lockdown would be in place, a decision was taken to review the data collected to date, to determine if it was feasible to halt any further data collection. The table below shows the target and achieved samples at baseline and 4 months as of 06/04/2020

WS3+ (Total Target: 246):

|  | MCT + CR | | | CR | | |
| --- | --- | --- | --- | --- | --- | --- |
|  | Target sample | Achieved sample | Number known to have completed CR | Target sample | Achieved sample | Number known to have completed CR |
| Baseline | 123 | 119 | - | 123 | 121 | - |
| 4 months FU | 98 | 76 (84)* | 58 | 98 | 100 (105)* | 61 |
| *including patients who returned the primary outcome (HADS) only | | | | | | |

On the basis of the samples for which the primary outcome at 4-months was available (MCT+CR=84; CR=105), the available power to detect the target effect of 0.4 was computed to be 88%. For the secondary outcomes (MCT+CR=76; CR=100) the power to detect an effect of 0.4 was 86%.

On the basis of the above, in discussion with the TSC it was decided that recruiting additional participants into WS3+ would have quite limited benefit, and that study resources would be better deployed at aiming to collect the outstanding 4 month FUs from current participants. This should also aim to reduce the imbalance between trial arms in the numbers with outstanding 4-month FUs to collect.

1. **Main analyses of Primary Outcomes**

*Research Null hypothesis:*

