**Planned statistical methods**

Test of the intervention: The effect of the intervention will be examined using the treatment group by time-point interaction term from a multi-level, mixed effects, regression model analysis combining both time-points (baseline and 4 months). The primary endpoint is HADS total score at 4 months, for which the interaction component relating to 4 months (relative to baseline) will be used.

The primary analysis will take the form of an intention-to-treat analysis using complete cases. This will be supplemented by a sensitivity analysis using multiple imputation, allowing us to assess the robustness of the results against missing values (see below). Other sensitivity analyses will be conducted as appropriate (see below). Analysis will be conducted using Stata 15 and an alpha level of 5%.

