**Planned statistical methods**

Analysis of secondary outcomes:

All of the secondary outcomes will be treated as longitudinal continuous variables. For each secondary outcome, the effect of the intervention will be examined using the 4-month trial arm by time-point interaction term from the mixed effects model. The model will have two levels: time-points within patients. Random effects will be applied to the patient-specific intercepts.

- Fixed effects: trial arm, time-point, arm x time-point, design variables (hospital site, sex), other pre-specified covariates and additional covariates (see Choice of Covariates, below).
- Random effects: patient.

Sensitivity analysis

See relevant section below

Alternative tests if violation of distributional assumptions

See distributional tests below.

1. **Sensitivity analysis**

All of the above primary and secondary analyses will be supplemented with at least one sensitivity analysis where appropriate.

Imputation methods will be used to impute missing values at both time points and the main analysis re-run using this data. Imputation will be done in two stages: first, missing baseline values will be imputed using all available variables at baseline, but excluding treatment arm; second, missing values at 4 months follow-up will be imputed, using the full set of variables and including the interaction term between treatment arm and time-point (for consistency with the analysis model). If missing data at baseline is under 5% these will be imputed with simple regression imputation, otherwise multiple imputation. Follow-up values will utilise multiple imputation.

The extent of the missing data will determine how many MI datasets will be generated.

Additional sensitivity analyses will be conducted where the outcome variable does not match the distributional assumptions of the model, and/or if trial-arm imbalance on multiple covariates is present.

1. **Distributional tests**

The distribution of each outcome variable will be examined. If for any of these, their measure of skewness or kurtosis exceeds 1 we will consider them non-normal and p-values will be validated using a bootstrap method (see Bootstrapping, below).

1. **Bootstrapping**

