Bootstrapping of standard errors will be applied for any non-normal outcome variable and p-values and 95% confidence intervals derived using these. To enable bootstrapping we will use Stata to generate a set of pseudorandom numbers to act as seeds for each bootstrap analysis; providing there are enough non-normal outcomes to justify this.

1. **Choice of covariates**

The covariates to be included in all primary and secondary analyses will be selected as described below.

A pre-specified group of covariates will be included as listed in Table 1. This list includes the study “design factors”, used as part of the stratification procedure for randomising allocation to trial arms (hospital site and gender), plus two variables considered prognostic of the outcomes: age and current anxiety/depression medication.

Table 2 lists additional available covariates. We will look for imbalance between trial arms on each of these and include those with a standardised mean difference between arms of >0.25 in the primary analysis model. Some categories within variables may be collapsed; the choices here will be determined by descriptive analysis of baseline values prior to any endpoint analysis.

| **Table 1** | |
| --- | --- |
| **Pre-specified covariates** | **Description** |
| Gender (design factor) | Two levels |
| Hospital site (design factor) | Categorical |
| Age | Continuous |
| Medication for depression or anxiety | Never taken/Currently taking/Taken in the past |

| **Table 2** | | |
| --- | --- | --- |
| **Additional available covariates** | **Description** | |
| Highest qualification | Categorical |  |
| BMI | Continuous | |
| Ethnicity | Categorical | |
| Marital status | Two levels: Married/in relationship versus single | |
| Time from baseline to measurement (in days) | Continuous | |
| Employment status | Categorical | |
| Smoking status | Never/Passive/Ex/Smoker | |
| Alcohol units per month | Continuous | |
| Age at first cardiovascular event | 0-18, 19-24, 25-33, 34-44, 45-54, 55-64, 65 or older | |
| Number of co-morbidities | Continuous | |
| Number of different previous cardiovascular event | Continuous | |
| Psychological therapies for anxiety or depression | Never received/Currently receiving/Received in the past | |

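### Covariates that are constant within a patient enter the two-row model without covariate × time-point terms, so in complete cases they leave the arm × time-point estimate and its standard error unchanged.

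*SAP*

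**What the plan says.** Under Analysis method, the primary outcome is HADS total at baseline and at 4 months, so each patient contributes two rows. Time-point is discrete and there is a random intercept per patient. The model terms are "Fixed effects: trial arm, time-point, arm x time-point, design variables (hospital site, sex), other pre-specified covariates and additional covariates". The covariance is chosen between unstructured and first-order autoregressive by BIC. Under Planned statistical methods for the primary outcome, the result is the 4-month interaction component relative to baseline, from an intention-to-treat analysis of complete cases.

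The secondary outcomes use the same model: "the effect of the intervention will be examined using the 4-month trial arm by time-point interaction term from the mixed effects model".

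Choice of covariates pre-specifies the design factors (site and gender) plus "two variables considered prognostic of the outcomes: age and current anxiety/depression medication". It also brings into the primary model any Table 2 variable whose standardised mean difference between arms exceeds 0.25.

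Under Sample size, the trial was "powered to detect an effect size of 0.4 on total HADS score at 90% power", with a baseline to follow-up correlation of 0.5 and 20% drop-out. The target was a total "of 123 per arm, aiming to collect 4month FU on 98 of these in each arm".

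**The concern.** The section on covariates has an evident purpose: to allow for prognostic variables and for chance imbalance when the arms are compared. The interaction term, however, is a within-patient contrast, 4 months minus baseline. A term that adds the same amount to both rows of a patient has no influence on that contrast.

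If so, the rule for adding imbalanced covariates has no effect on the primary estimate for any variable fixed at baseline. A reader of the results could take the estimate to be adjusted for these variables when the listing has not changed it. Chance imbalance in a variable that predicts change would stay in the estimate, and any precision that the covariates could offer would be lost. The same applies to every secondary outcome.

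**Working it through.** **Inputs from the SAP.** Effect 0.4 SD, power 90%, correlation ρ = 0.5, drop-out 20%, alpha 5%. Follow-up numbers are 84/105 for the primary outcome (stated power 88%) and 76/100 for the secondary outcomes (stated power 86%). Assumptions here: the alpha is two-sided (the SAP does not say), and a complete case has both rows present.

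**1. The SAP's own figures.** They reproduce with the baseline-adjusted (ANCOVA) variance 1 - ρ² = 0.75.
- n per arm = 2(1.960 + 1.282)² × 0.75 / 0.4² = 98.5 (stated 98). Recruitment: 98 / 0.8 = 122.5, rounded up to 123 (stated 123).
- At 84/105: SE = √0.75 × √(1/84 + 1/105) = 0.866 × 0.1464 = 0.1268. Power = Φ(0.4/0.1268 - 1.960) = 88.4% (stated 88%).
- At 76/100: 85.9% (stated 86%).

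**2. Why the covariates cancel.** With covariates x constant within patient:
- Baseline: E[Y0] = a + b·arm + g·x
- 4 months: E[Y1] = a + b·arm + c + d·arm + g·x
- Difference: E[Y1 - Y0] = c + d·arm

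The term g·x is gone. What remains of the data, uncorrelated with the difference, has its own free intercept and arm coefficient, so it carries no information about d. The estimate of d is the raw difference in mean change, whatever x is. This holds for a random intercept and for an unstructured 2 × 2 covariance. With two time-points, AR(1) has the same form as an exchangeable covariance. The BIC choice therefore makes no difference here.

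**3. Numerical check of the cancellation.** REML random-intercept models were fitted to 12 simulated data sets of 84/105 complete pairs, and again with drop-out dependent on the covariate. Adding the covariate main effects changed the estimate by at most 3 × 10⁻¹⁵ and its SE by at most 1.4 × 10⁻⁶, which is numerical noise. A separate run of 60 data sets agreed. One data set fitted with an unstructured covariance gave -0.229868 (SE 0.202284) with and without the covariate, equal to the raw difference in change.

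**4. Size of what is left uncorrected.** Assumed: true effect -0.40, and a covariate that predicts change and is 0.3 SD higher in one arm. Mean estimates over the 12 data sets:

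| Model | Mean estimate |
|---|---|
| No covariates | -0.313 |
| Covariates as planned | -0.313 |
| Covariate × time-point added | -0.397 |

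Across the runs, the first two rows lay at about -0.31 to -0.33. Covariate × time-point terms or ANCOVA gave about -0.40. The shift is the imbalance times the slope of change on the covariate. Here 0.397 - 0.313 = 0.084, and 0.084 / 0.3 = 0.28 per SD. With the same slope, an imbalance at the SAP's threshold would leave 0.25 × 0.28 = 0.07.

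**5. Power of the planned contrast.** The variance of a change is 2(1 - ρ) = 1.
- At 84/105: Φ(0.4/0.1464 - 1.960) = 78.0%.
- At 98/98: 80.0%. At 76/100: 74.8%.
- For 90% power: 2(1.960 + 1.282)² / 0.4² = 131.3, so 132 followed up, and 132 / 0.8 = 165 recruited per arm.
- If covariate × time-point terms explained an assumed 5% to 10% of the variance of change, power at 84/105 would be 80.1% to 82.1%.

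**The case against.** A reader might infer that the planned adjustment has no effect anywhere in the trial, that the result is wholly unadjusted, or that the test is invalid. The document does not support any of these.

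- **Not every listed covariate is constant.** Days between baseline and measurement, in Table 2, is zero at baseline and varies at 4 months. Entered as time-varying, it does move the estimate, by about 0.02 on average in the simulated complete cases.
- **Complete cases are not defined.** If baseline-only rows were kept (119/121 at baseline), the main effects would move the estimate by 0.017 on average with random drop-out and by 0.033 with drop-out dependent on the covariate (maximum 0.056), against an SE of about 0.147. Under random drop-out this did not correct the imbalance: mean -0.324, against -0.407 with covariate × time-point terms. Missing covariate values could also change which patients are analysed.
- **The change contrast already does some of the work.** It removes any covariate effect that is equal at both time-points. Only variables that predict change matter, and the SAP gives no evidence that any listed variable does. Under randomisation, such imbalance does not bias the estimator over repeated trials.
- **Other analyses exist.** In the multiple-imputation analysis, covariates act through the imputation. The SAP also promises further sensitivity analyses if several covariates are imbalanced, but it does not give their form, so this does not repair the primary analysis.
- **The SAP does not claim a precision gain**, and it has no text on how the adjustment would be reported. Its intent to allow for imbalance is an inference, though a fair one.
- **Most of the possible power gain comes from baseline adjustment**, not from the covariates: 78.0% to 88.4% with ANCOVA, against 80.1% to 82.1% from covariate × time-point terms.

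These points limit the reach of the concern. None restores the function of the patient-constant covariates in the complete-case analysis.

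**Conclusion.** The point holds in this form. In the complete-case two-row model for the primary and secondary outcomes, covariates constant within patient leave the arm × time-point estimate and its SE unchanged under all the covariance structures that the SAP considers. The 0.25 rule and the prognostic covariates therefore cannot correct chance imbalance in variables that predict change, or gain precision.

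The cancellation is exact. It rests on complete pairs and on reading the list of fixed effects as main effects, which is the natural reading because arm × time-point is the only interaction written out. The sizes are illustrative: an uncorrected shift of about 0.08 for an assumed 0.3 SD imbalance with a slope of 0.28 on change. The power comparison (about 78% planned, 88% stated, at 84/105) rests on the SAP's correlation of 0.5 and a two-sided 5% test. The plan should be changed, but no invalid test or systematic bias follows from it.

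**What to change.** For the primary and secondary outcomes, replace the two-row model with ANCOVA of the 4-month score on arm, baseline score and the covariates that the SAP already lists. The covariates then act on the outcome that is compared. The model also matches the baseline-adjusted variance behind the stated sample size and power.

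If the two-row model is kept, add a covariate × time-point term for each covariate. This makes the adjustment work but recovers only part of the power difference.

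In either case, define a complete case and say how days between baseline and measurement would enter. The cost is SAP wording and a few degrees of freedom, small against 84 + 105 = 189 patients. No further data are needed.

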**Planned statistical methods**

Analysis of secondary outcomes:

All of the secondary outcomes will be treated as longitudinal continuous variables. For each secondary outcome, the effect of the intervention will be examined using the 4-month trial arm by time-point interaction term from the mixed effects model. The model will have two levels: time-points within patients. Random effects will be applied to the patient-specific intercepts.

- Fixed effects: trial arm, time-point, arm x time-point, design variables (hospital site, sex), other pre-specified covariates and additional covariates (see Choice of Covariates, below).
- Random effects: patient.

Sensitivity analysis

See relevant section below

Alternative tests if violation of distributional assumptions

See distributional tests below.

1. **Sensitivity analysis**

All of the above primary and secondary analyses will be supplemented with at least one sensitivity analysis where appropriate.

Imputation methods will be used to impute missing values at both time points and the main analysis re-run using this data. Imputation will be done in two stages: first, missing baseline values will be imputed using all available variables at baseline, but excluding treatment arm; second, missing values at 4 months follow-up will be imputed, using the full set of variables and including the interaction term between treatment arm and time-point (for consistency with the analysis model). If missing data at baseline is under 5% these will be imputed with simple regression imputation, otherwise multiple imputation. Follow-up values will utilise multiple imputation.

The extent of the missing data will determine how many MI datasets will be generated.

Additional sensitivity analyses will be conducted where the outcome variable does not match the distributional assumptions of the model, and/or if trial-arm imbalance on multiple covariates is present.

1. **Distributional tests**

The distribution of each outcome variable will be examined. If for any of these, their measure of skewness or kurtosis exceeds 1 we will consider them non-normal and p-values will be validated using a bootstrap method (see Bootstrapping, below).

1. **Bootstrapping**

Bootstrapping of standard errors will be applied for any non-normal outcome variable and p-values and 95% confidence intervals derived using these. To enable bootstrapping we will use Stata to generate a set of pseudorandom numbers to act as seeds for each bootstrap analysis; providing there are enough non-normal outcomes to justify this.

1. **Choice of covariates**

The covariates to be included in all primary and secondary analyses will be selected as described below.

A pre-specified group of covariates will be included as listed in Table 1. This list includes the study “design factors”, used as part of the stratification procedure for randomising allocation to trial arms (hospital site and gender), plus two variables considered prognostic of the outcomes: age and current anxiety/depression medication.

Table 2 lists additional available covariates. We will look for imbalance between trial arms on each of these and include those with a standardised mean difference between arms of >0.25 in the primary analysis model. Some categories within variables may be collapsed; the choices here will be determined by descriptive analysis of baseline values prior to any endpoint analysis.

| **Table 1** | |
| --- | --- |
| **Pre-specified covariates** | **Description** |
| Gender (design factor) | Two levels |
| Hospital site (design factor) | Categorical |
| Age | Continuous |
| Medication for depression or anxiety | Never taken/Currently taking/Taken in the past |

| **Table 2** | | |
| --- | --- | --- |
| **Additional available covariates** | **Description** | |
| Highest qualification | Categorical |  |
| BMI | Continuous | |
| Ethnicity | Categorical | |
| Marital status | Two levels: Married/in relationship versus single | |
| Time from baseline to measurement (in days) | Continuous | |
| Employment status | Categorical | |
| Smoking status | Never/Passive/Ex/Smoker | |
| Alcohol units per month | Continuous | |
| Age at first cardiovascular event | 0-18, 19-24, 25-33, 34-44, 45-54, 55-64, 65 or older | |
| Number of co-morbidities | Continuous | |
| Number of different previous cardiovascular event | Continuous | |
| Psychological therapies for anxiety or depression | Never received/Currently receiving/Received in the past | |

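### Allocation was stratified by site, gender and anxiety/depression/both, but the models carry only site and gender, which makes the arm by time-point test mildly conservative

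*SAP*

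**What the plan says.** Under Sample size, the SAP describes allocation in "randomised blocks of size 6 and 4" and says that the sequence was "stratified by site, gender and whether they suffered from anxiety, depression or both". It adds that "WS3+ utilised an identical randomisation procedure". Three stratifiers therefore apply to the whole combined sample, pilot and extension.

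The analysis sections name two:

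- Primary model (Analysis method): "Fixed effects: trial arm, time-point, arm x time-point, design variables (hospital site, sex"), followed by the other covariates.
- Secondary models (Planned statistical methods): "design variables (hospital site, sex), other pre-specified covariates and additional covariates".
- Choice of covariates: the design factors are those "used as part of the stratification procedure for randomising allocation to trial arms (hospital site and gender"). The only other covariates fixed in advance are age and medication for depression or anxiety. Table 1 marks only gender and hospital site as design factors.

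Table 2 lists the variables that may enter if the standardised mean difference between arms exceeds 0.25. The anxiety/depression/both category is not among them, so that rule cannot admit it. Medication (Table 1) and psychological therapies (Table 2) are different variables.

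**The concern.** The plan's evident principle is that factors used to stratify the randomisation enter every model. It then applies that principle to two of its three stratifiers without explanation.

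Stratified blocks make the arms more alike on the stratifier than simple randomisation would. If the stratifier also predicts the quantity being compared, the treatment estimate varies less from trial to trial than a model without the stratifier assumes. The reported standard error is then too large, the confidence interval too wide and the test conservative. The trial stopped recruiting at a computed 88% power for the primary outcome, so an avoidably wide interval is worth removing.

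**Working it through.** **1. The plan's own figures.** Inputs from Sample size: effect 0.4 SD, 90% power, correlation 0.5, 20% drop-out. Two-sided 5% is assumed, because sidedness is not stated.

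- n per arm = 2 × (1 − 0.5²) × (1.960 + 1.282)² / 0.4² = 98.5, against 98 stated.
- 98 / 0.8 = 122.5, so 123 recruited per arm, as stated.
- Power is 88.4% for 84 v 105 and 85.9% for 76 v 100, against 88% and 86% stated.

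The figures reproduce. The calculation has no stratum term, so the omission does not make them wrong.

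**2. What a main effect does in the planned model.** For patient i with patient-level covariates x:

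- baseline: y0 = a + g·x + c·arm + u + e0
- 4 months: y1 = a + t + g·x + c·arm + d·arm + u + e1
- difference: y1 − y0 = t + d·arm + (e1 − e0)

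The terms g·x and u cancel. With complete pairs, the arm by time-point estimate d is the difference in mean change, and a stratum main effect cannot alter it. A stratum by time-point interaction stays in the difference and can.

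**3. Size by formula, one illustrative set of inputs (assumed).** Total 240 patients, 120 per arm. Stratum shares are 0.4, 0.2, 0.4 and baseline stratum means −0.6, −0.4, 0.8 in SD units. The SD is 1 at both times and b is the slope of follow-up on baseline.

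- Share of baseline variance between strata: 0.4 × 0.36 + 0.2 × 0.16 + 0.4 × 0.64 = 0.432.
- Variance of change: 2(1 − b). The part between strata is (1 − b)² × 0.432, so the share is (1 − b) × 0.432 / 2.
- b = 0.5: share 0.108. SE without stratum √(1 × 4/240) = 0.129; with stratum by time-point √(0.892 × 4/240) = 0.122. Excess 1/√0.892 − 1 = 5.9%.
- b = 0.7: share 0.065. Excess 1/√0.935 − 1 = 3.4%.

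A 5.9% excess moves the critical value from 1.96 to 1.96 × 1.059 = 2.08 on the true scale, a type I error of about 3.8%.

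**4. Simulation with the same inputs, b = 0.5.**

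| Follow-up | SE, no stratum | + main effect | + stratum by time-point |
|---|---|---|---|
| Complete (60 runs, no effect) | 0.129 | 0.129 | 0.122 |
| 29% / 13% missing (70 runs, effect 0.4) | 0.142 | 0.139 | 0.132 |

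With complete pairs, the main effect changed the estimate by 0.000. The empirical SD of the estimate was 0.122 under all three models, so the gain lies in the reported error bar. The missing rates follow from the achieved counts: (119 − 84)/119 = 29% and (121 − 105)/121 = 13%.

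**5. Simulation with strata from a subscale cut-off of 8 (assumed).** 240 patients, five sites (assumed), blocks of 4 and 6 within site by sex by stratum, 3,000 null trials per scenario, change-score form.

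| HADS total | SE excess | Type I error |
|---|---|---|
| Slope 0.5, complete | 7.0% | 3.5% |
| Slope 0.7, complete | 4.1% | 4.0% |
| Slope 0.5, 29% / 13% missing | 4.4% | not reported |

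At slope 0.5 with complete pairs, adding the stratum to the change contrast cut the model SE from 0.612 to 0.572 (6.5%) and brought type I error to 4.7%. Other runs gave 6-9% at slope 0.5 and, in a smaller set of 1,000 trials, 1-2% at slope 0.7. The overall range is roughly 2-9%.

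**6. ANCOVA for comparison.** In the step 4 simulation with complete follow-up, regressing the 4-month score on arm and baseline gave a model SE of 0.1117 without the stratum and 0.1119 with it. There was no gain.

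**The case against.** The strongest reply is that adding the factor in the form the SAP uses for its other covariates, as a main effect, achieves nothing with complete pairs. Step 2 shows that this is right, and the primary analysis is declared to use complete cases. Site and sex as listed cancel in the same way. This limits the remedy to the interaction form. It does not remove the discrepancy or the conservative standard error.

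A second reply is that the inputs are assumed. The SAP does not say how anxiety, depression or both was defined, and it gives no stratum shares and no relation to change. This also stands, so the size can only be a range. Simulation noise adds to it: with 1,000 runs, a type I error near 5% has a Monte Carlo standard error of 0.7 points, so small differences in the smaller runs should not be read closely.

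Some stronger inferences are tempting, and the document does not support them:

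- *The analysis ignores the stratifier most related to HADS.* The link is plausible, since HADS measures anxiety and depression, but the SAP gives no figure for it. Baseline HADS is also in the primary model as an outcome row, so baseline severity is not wholly absent.
- *The secondary outcomes suffer most.* In the step 5 setting, the SE excess was 6.1% for HADS depression and 2.9% for HADS anxiety, against 7.0% for the total. The non-HADS outcomes were not simulated in those runs.
- *One extra line in Table 1 cures it.* Step 2 shows that it does not.

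**Conclusion.** The inconsistency is plain from the text and needs no assumption: three stratifiers at randomisation, two in the analysis, no reason given, and no route by which the third could enter. The consequence is modest. In the planned two-time-point model, the standard error for HADS total is roughly 2-9% too large. This assumes 240 patients, strata cut at 8 on the subscales, a slope between 0.5 and 0.7, and follow-up that is complete or missing at the achieved rates. The test errs on the cautious side. The treatment estimate is not biased and false positives are not increased. The point is worth correcting because the change is nearly free, but it does not threaten the trial's conclusion.

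**What to change.** 1. In Choice of covariates, correct the sentence on design factors to name all three, and add the three-level factor, as used at randomisation, to Table 1.
2. In the primary and secondary model specifications, include the factor with its time-point interaction. State also whether site and sex are crossed with time-point, because their main effects cancel in the same way.
3. If the analysis is instead an ANCOVA on baseline HADS, list the factor there too. This keeps the analysis consistent with the design, but essentially no precision should be expected from it for the HADS outcomes.
4. If the factor is to stay out, say why.

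The cost is about four degrees of freedom (two for the main effect, two for the interaction), plus edits to one table and three short passages. The variable was recorded at randomisation, so no new data are needed.
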